## 2. Background

### i. Introduction

Aortic arch repair is a complex operation which requires specialised neuroprotective strategies when arteries supplying the brain with blood are temporarily occluded during the repair. Reducing cerebral metabolism via hypothermia protects against the effects of cortical ischaemia and optimal cerebral protection is thought to occur during periods of electro-cerebral inactivity (ECI) as measured via EEG.

ECI, defined as  $<2\mu\text{V}$  EEG activity for a 3-minute period, occurs at core temperatures between  $28-12^{\circ}\text{C}$ . Sixty percent of adults achieve ECI at  $18^{\circ}\text{C}$ , the temperature used by the BCH team, but recent data in infants suggests more variability. Without EEG, multisite temperature monitoring is recommended to ensure adequate brain cooling (class 1 recommendation, level B evidence) but time to ECI, and cortical temperature, are not precisely predictable from oesophageal or nasopharyngeal temperature (temperature monitors used at BCH).

Up to 20% of potential study participants will develop sub-clinical seizures perioperatively, and the only way to detect these is via EEG. Preoperative EEG may help identify which patients are more likely to require specialized neuroprotection as certain patterns will highlight central nervous system abnormalities. Although there is currently insufficient evidence to support routine EEG monitoring for the study population in question it is feasible that:

- Preoperative EEG could identify patients at high risk of neurological complications.
- There may be inter-individual variation in the degree of hypothermia required to achieve ECI, and thereby optimal neuroprotection.
- Postoperatively, a substantial proportion of patients may develop subclinical seizures which go undetected in the absence of EEG monitoring and are associated with adverse neurological outcome.

### ii. Rationale & objectives

The addition of perioperative EEG for neonates undergoing aortic arch repair could ensure that:

- Those with abnormalities detected via EEG are identified preoperatively.
- Hypothermia is not excessive beyond the point of ECI, which has been reported to predict poor neurodevelopmental outcome.
- Current practice is sufficient to provide optimal neuroprotection.
- Perioperative subclinical seizures are identified and treated in a timely manner.

Currently there is a lack of evidence in this field which this study will contribute to.

The objectives of the study are to:

1. Evaluate whether the temperature at which ECI on EEG is achieved is a modifiable risk factor associated with the long-term neurodevelopmental outcomes of neonates undergoing aortic arch surgery with deep hypothermic circulatory arrest (DHCA).
2. Report perioperative EEG patterns, seizure burden, and neurodevelopmental outcome in this previously unmonitored group.

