## 1. Protocol summary

### **Title: Surgery on the aortic arch and feasibility of EEG (SAFE) monitoring**

**Population:** Target population is all neonates ( $\leq 4$  weeks corrected age) requiring aortic arch surgery at Birmingham Children's Hospital (BCH).

**Study duration:** Participants are enrolled at one time point and provide electroencephalography (EEG) data for analysis and use in future research projects. The study will finish September 2028.

**Aim:** To identify if EEG monitoring can be used to optimise neuroprotection perioperatively and therefore contribute to risk reduction. We will do this by tracking temperature-dependent changes in brain electrical activity during cooling to 18 degrees Celsius (the temperature used by BCH team) in neonates undergoing aortic arch repair, and identify the temperature at which electro-cerebral inactivity (ECI) is achieved. Pre- and Post-operative EEG will be recorded to identify groups which require increased perioperative resource.

**Primary objective:** To evaluate whether the temperature at which ECI on EEG is achieved is a modifiable risk factor associated with the long-term neurodevelopmental outcomes of neonates undergoing aortic arch surgery with deep hypothermic circulatory arrest (DHCA).

**Secondary objectives:** To report perioperative EEG patterns, seizure burden, and neurodevelopmental outcome in this previously unmonitored group.

**Funding:** HEE/NIHR Doctoral Clinical and Practitioner Academic Fellowship (NIHR302896) awarded to [name] (2023-2026). The follow-up sub-study is funded by a research grant from Birmingham Women's and Children's Hospital Charity (37-6-206).

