#### **Known potential risks**

The procedures involved in the study are routine, involve minor risks only and do not alter patient management. The risk of EEG includes skin abrasions and mild discomfort during electrode application, which will be minimised by ensuring only qualified staff apply electrodes.

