## 5. Outcomes measures

### i. Primary outcome

The proportion of participants who achieve ECI during cooling before the start of DHCA, and in these, the temperature (degrees Celsius) and variability ( $\pm$ SD) at which ECI is achieved.

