### ii. Secondary outcomes

- The relationship between whether or not ECI is achieved during cooling before DHCA and clinical outcome measures.
- The duration of ECI (minutes) and its relationship with clinical outcome measures.
- The morphology, amplitude and continuity of EEG activity during hypothermia, DHCA, selective antegrade cerebral perfusion (SACP) and rewarming to normothermia.
- Pre- and postoperative background EEG patterns and seizure burden (absent, present, status epilepticus). This will be assessed retrospectively by specialist clinical neurophysiologists, with reference to published articles.

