**Appendix: SAFE-Follow-up assessment of Infant Neurodevelopment (SAFE-FIN) sub-study**

**Population:** All neonates ( $\leq 4$  weeks corrected age) recruited to the SAFE Monitoring study at BCH in whom consent for future contact for determining development was obtained.

**Study duration:** With consent, the parents or guardians of participants will be re-approached at 22-26 months following surgery for a single assessment of neurodevelopment.

**Aims:** To 1) identify whether perioperative EEG activity is associated with long-term neurodevelopmental outcome, 2) assess feasibility of conducting follow-up neurodevelopmental assessments in this population.

**Primary objective:** Assess neurodevelopmental outcome following aortic arch surgery in neonates approximately 24 months post procedure using the Bayley-III scale of infant development.

**Secondary objectives:** Evaluate whether the duration of electrocerebral inactivity (ECI), or not achieving ECI prior to deep hypothermic circulatory arrest (DHCA); seizure burden and other EEG patterns are associated with Bayley-III scores. We will also determine whether late follow-up neurodevelopmental assessments are feasible in this population.

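### Temperature at ECI is the infant's response to cooling; with one described cooling temperature it can hardly be separated from depth of cooling beyond ECI, so the primary objective can show association but not a modifiable risk factor

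*Protocol*

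**What the plan says.** Protocol section 2.ii lists four things that perioperative EEG could secure. One of them is "Hypothermia is not excessive beyond the point of ECI, which has been reported to predict poor neurodevelopmental outcome". The first objective in the same section, which is also the primary objective in section 1, is to "Evaluate whether the temperature at which ECI on EEG is achieved is a modifiable risk factor associated with the long-term neurodevelopmental outcomes".

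The Aim in section 1 describes recording "during cooling to 18 degrees Celsius (the temperature used by BCH team) in neonates undergoing aortic arch repair". Section 2.i repeats 18 °C as the team's temperature, and no other cooling level appears. Under Known potential risks (section 2.iii), the study procedures "involve minor risks only and do not alter patient management".

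The primary outcome (section 5.i) is the proportion reaching ECI before deep hypothermic circulatory arrest (DHCA) and, in those infants, "the temperature (degrees Celsius) and variability ( $\pm$ SD) at which ECI is achieved". The secondary outcomes (section 5.ii) include "The duration of ECI (minutes) and its relationship with clinical outcome measures". The SAFE-FIN appendix has a secondary objective relating ECI duration, or failure to reach ECI before DHCA, to Bayley-III scores. Section 7 treats the secondary outcomes as exploratory. Neither the main study nor the appendix names, as an outcome, the temperature at the start of DHCA or the number of degrees cooled below ECI.

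**The concern.** The exposure in the rationale and the exposure in the objective differ. The rationale concerns cooling carried past ECI, which a team controls. The objective concerns the temperature at which a given brain falls silent. Section 2.i itself treats this as varying between infants. In an observational cohort it is a patient characteristic revealed by cooling, and nobody sets it.

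The two are also tied together by the design. If all infants are cooled towards the same end temperature, one who becomes inactive at a warmer temperature is necessarily cooled further beyond that point. Suppose warmer ECI goes with poorer Bayley-III scores. One explanation is that a vulnerable brain goes quiet early; another is that the infant was cooled too far past ECI. Both predict nearly the same data. Reporting the first objective as written, with the word modifiable, would favour the second explanation without evidence for it.

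**Working it through.** **Inputs.** From Protocol section 7: 17 of 30 feasibility-phase infants reached ECI before DHCA, with mean ECI temperature 22.6 °C and SD 2.9 °C; 74 are to be recruited and 41 are expected to reach ECI. From sections 1 and 2.i: cooling temperature 18 °C. Achieved end temperatures and their spread are not given, so their SD is assumed over a range.

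**1. The plan's own figure.** The half-width of the 95% interval for mean ECI temperature is 1.96 × 2.9 / √41 = 0.89 °C (0.92 °C with the t quantile). Both round to the stated ±0.9 °C. The expected count is 74 × 0.56 = 41.4, in line with 41. The precision statement reproduces and is not in question.

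**2. Depth below ECI.** Let D = T_ECI − T_end. With T_end = 18 °C, mean D = 22.6 − 18 = 4.6 °C and SD 2.9 °C. This describes only infants who reached ECI before DHCA. For the other 13 of 30 (43%), and for about 74 − 41 = 33 of the planned cohort, D before arrest does not exist.

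**3. Separability.** If T_end is constant, D is T_ECI minus a constant and the correlation is exactly 1. If T_end varies independently of T_ECI,

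corr(T_ECI, D) = 2.9 / √(2.9² + SD_end²), and VIF = 1 / (1 − r²) = (2.9² + SD_end²) / SD_end².

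| Assumed SD_end (°C) | r | VIF | Standard error multiplied by √VIF |
|---|---|---|---|
| 0 | 1.000 | infinite | not estimable |
| 0.5 | 0.985 | 34.6 | 5.9 |
| 1 | 0.945 | 9.4 | 3.1 |
| 1.5 | 0.888 | 4.7 | 2.2 |
| 2 | 0.823 | 3.1 | 1.8 |

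Independence is an approximation. Reaching ECI before DHCA requires T_ECI to be at or above the temperature at arrest, and a positive link between T_ECI and T_end would lower r.

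**4. Information available.** With 41 infants, the smallest single correlation detectable with 80% power (two-sided 5%) is tanh[(1.96 + 0.84) / √38] = 0.43, before any loss to follow-up at two years. That is for one exposure alone. Putting T_ECI and depth in the same model adds the inflation in the table.

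**5. What the listed outcomes offer.** ECI duration is the one listed measure of exposure beyond ECI. It is not fixed by the end temperature, since it also reflects cooling rate, arrest time and rewarming time. It is not free of the problem either: an infant inactive at a warmer temperature crosses the threshold earlier on the way to the same end point and, other things equal, accumulates more ECI time.

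**The case against.** The strongest reply is that the protocol already addresses exposure beyond ECI. ECI duration is a secondary outcome, and the appendix relates it to Bayley-III. This stands against a stronger reading that a reader might draw, namely that nothing at all can be learned about excess hypothermia. The documents do not support that reading. Duration bears on the question, though as an exploratory measure of time and not of depth.

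A reader might also infer that every infant ends at exactly 18 °C and that the correlation of 1 is a fact about this cohort. The protocol gives 18 °C as the team's temperature and reports no achieved values. The figure of 1 follows from assuming a constant end point, and the range in the table is the fairer statement.

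Nor is over-cooling the declared study hypothesis. It is one of four rationale points, and much of the planned analysis compares infants with and without ECI before DHCA. It is, however, the one rationale point that explicitly ties cooling relative to ECI to poor neurodevelopment, which is the subject of the primary objective.

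Finally, the temperatures are already recorded (section 4.i) and the EEG is synchronised to the monitor clock (section 1), so derived variables could be left to an analysis plan. That is fair for the variables taken alone, and their absence is not an error in itself. It does not answer the main point: the objective is worded in the protocol, and no later model can create variation in cooling that the cohort lacks.

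**Conclusion.** The point holds in a limited form. As designed, the study can show whether ECI temperature is associated with later development. It cannot show that ECI temperature, or the cooling depth that goes with it, is modifiable in the sense the primary objective implies. Depth and ECI temperature are inseparable under a constant end temperature. They remain highly collinear (r about 0.985 to 0.823) for an assumed end-temperature SD of 0.5 to 2 °C, taken as independent of ECI temperature and with the feasibility SD of 2.9 °C. The statement about depth applies only to infants with ECI before DHCA. The exploratory ECI-duration analyses remain as partial evidence on excess hypothermia. The wording should be changed; the data collection and the precision calculation in section 7 are unaffected.

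**What to change.** - **Sections 1 and 2.ii:** remove the description of ECI temperature as a modifiable risk factor, so that the objective asks whether it is associated with neurodevelopment. Add that, under a single cooling target, any such association is prognostic and does not show cooling depth to be a modifiable cause.
- **Section 5.ii, all infants:** add the recorded temperature at the start of DHCA as an exploratory variable. It also shows whether infants without ECI were arrested at a warmer temperature or stayed active at the target.
- **Section 5.ii, infants with ECI before DHCA only:** add degrees below ECI at the start of DHCA (ECI temperature minus temperature at DHCA start) as an exploratory variable, reported beside ECI duration.
- **Do not** make the correlation of depth with ECI temperature an outcome. Depth contains ECI temperature by construction, so a high value is largely built in and tells the reader little.

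The cost is a protocol wording change and slightly more analysis from traces already recorded. The price is a more modest claim. Nothing here proposes a change in cooling practice.

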### **iii. Potential benefits and risks**

#### **Known potential benefits**

EEG interpretation may have clinical significance to the participant's care. Seizures, epileptiform activity, immaturity, evidence of hypoxic ischaemic encephalopathy (HIE), and Bayley-III scores will be disclosed to the clinical team looking after the participant. By improving our understanding of optimal neuroprotection during surgery, this study has the potential to improve the outcomes of future patients undergoing aortic arch repair.

#### **Known potential risks**

The procedures involved in the study are routine, involve minor risks only and do not alter patient management. The risk of EEG includes skin abrasions and mild discomfort during electrode application, which will be minimised by ensuring only qualified staff apply electrodes.

### **3. Recruitment**

#### **i. Study population**

Neonates ( $\leq 4$  weeks corrected age) undergoing surgical repair of the aortic arch with deep hypothermic circulatory arrest (DHCA), either as an isolated procedure or as part of a more complex congenital cardiac procedure, eg. Norwood operation for hypoplastic left heart syndrome.

#### **ii. Inclusion and exclusion criteria**

Inclusion criteria: Neonates ( $\leq 4$  weeks corrected age) undergoing aortic arch repair using cardiopulmonary bypass and DHCA, with occlusion of the head and neck arteries.

Exclusion criteria: Parent or guardian is unable or unwilling to provide informed consent.

#### **iii. Screening and participant enrolment**

Participants will be identified from the surgical waiting list by the PI and communicated to the research team via a secure messaging app (e.g. WhatsApp) in which key study collaborators will be included. The PI will know when the potential participant is due to come in (TCI) for the procedure and the date and time appropriate to seek informed consent. A Parent Information Sheet will be provided to the parent or guardian of potential study participants at least 12 hours before consent is sought. The PI will seek informed consent from the parent or guardian of study participants prior to surgery.

The parent or guardian is free to withdraw consent at any time without providing a reason. If at any time the parent or guardian request withdrawal, the data collected up until that time may still be included in the analysis. The PI will document study withdrawal in the medical notes.

#### 4. Procedures

##### i. EEG

All participants will have scalp electrodes applied in accordance with published guidelines, consisting of up to 23 electrodes, with a minimum of 15 (Figure 2). A collodion adhesive and micropore tape will secure electrodes to the scalp. Frontal electrodes will be placed equidistant between FP1/FP2 and F3/F4 if near infrared spectroscopy (NIRS) is used to monitor cerebral tissue oxygen saturation. EEG will be acquired via an ambulatory recording device [Morpheus Home LTM or SD LTM 64 Express, Micromed] and data will be coded with a unique study number and stored electronically on a secure part of the NHS Trust IT network. Temperature will be measured via a nasopharyngeal temperature probe and recorded via intellivue X monitors.

[figure not shown]

**Figure 2. Left: The international 10-20 system for EEG electrode placement. Right: a modified version for neonates. NB. A1 and A2 will not be applied. In addition to the diagrams, ground and reference electrodes will be placed in an “electrically neutral” location on the scalp; 2 ECG electrodes will be applied to the torso.**

##### ii. Clinical data collection

Participants’ CRF will be entered onto a secure electronic database within Birmingham Children’s Hospital (BCH). Offline/hard copies of CRFs will be stored within a research master site file located within the neurophysiology department of BCH. The CRF will be populated by the PI. Other routinely collected clinical variables will be obtained from the cardiac database. Research collaborators from the Neurophysiology department will assess pre- and postoperative EEG and seizure burden in accordance with previously published guidelines.

## 5. Outcomes measures

### i. Primary outcome

The proportion of participants who achieve ECI during cooling before the start of DHCA, and in these, the temperature (degrees Celsius) and variability ( $\pm$ SD) at which ECI is achieved.

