## 7. Sample size calculation

During the feasibility phase, 17/30 (56%) patients achieved ECI before DHCA at a mean temperature of 22.6°C (SD  $\pm$ 2.9). We estimate that by recruiting a total of 74 participants, 41 will achieve ECI before DHCA with the same mean temperature at ECI with a 95% confidence interval around the estimate of  $\pm$ 0.9°C. There is no robust data on the rate of the secondary outcomes in neonatal aortic arch repair so these will be considered exploratory.

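### The mean ECI temperature among neonates who reach ECI is a valid conditional summary, but it does not estimate the temperature needed for ECI, and read that way it is too warm

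*Protocol*

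**What the plan says.** Only the protocol is available; the points below are all fixed in it.

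- **Section 5.i (primary outcome)** has two parts: the proportion who reach ECI during cooling before DHCA, "and in these, the temperature (degrees Celsius) and variability" (as an SD) at which they reach it.
- **Section 7** sizes the study on the second part. In the feasibility phase "17/30 (56%) patients achieved ECI before DHCA at a mean temperature of 22.6°C", with SD 2.9. Of 74 recruited, "41 will achieve ECI before DHCA with the same mean temperature at ECI", "with a 95% confidence interval around the estimate of" ±0.9°C.
- **Section 1 (Aim)** is to track EEG during cooling to 18°C and "identify the temperature at which electro-cerebral inactivity (ECI) is achieved".
- **Section 2.i** gives 28 to 12°C as the range of core temperatures at which ECI occurs, and motivates the study with "There may be inter-individual variation in the degree of hypothermia required to achieve ECI, and thereby optimal neuroprotection".
- **Section 8** says the ECI temperature and its SD will inform the usefulness of EEG in cardiac surgery. It does not repeat the restriction to achievers.

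**The concern.** Cooling is aimed at 18°C, and the protocol's own range for ECI runs down to 12°C. A neonate whose EEG is still active at DHCA is therefore not uninformative about the ECI temperature. The natural reading is that this child's threshold lies below the lowest temperature reached, which makes it a censored observation. A mean and SD taken only in achievers leave out much of the cold end of the distribution.

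At stake is how the result will be read. A report of ECI at 22.6 ± 0.9°C could be taken as the degree of hypothermia neonates need, when about two in five had not reached ECI by DHCA. The SD, which is the natural measure of variation between neonates, would probably be too small for that purpose. Giving the proportion alongside tells the reader that some did not reach ECI, but it does not correct the mean, the SD or the interval.

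**Working it through.** **Inputs.** Section 7: 17 of 30 reached ECI, mean 22.6°C, SD 2.9; 74 to be recruited, 41 expected to reach ECI, half-width 0.9°C. Section 1: cooling to 18°C. Section 2.i: ECI between 28 and 12°C. Assumption: the floor c, meaning the lowest temperature non-achievers reached before DHCA. The protocol does not give it, so it is varied.

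**1. The plan's own figure.** 74 × 0.56 = 41.4, giving 41. Half-width = 1.96 × 2.9/√41 = 0.89, which matches ±0.9. Section 7 is arithmetically correct for the achievers' mean. (17/30 is 56.7%, printed as 56%; this is immaterial.)

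**2. How many give no temperature.** 30 − 17 = 13, and 13/30 = 43%. In the full study, 74 − 41 = 33.

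**3. Without a distributional model.** Put all 13 non-achievers' thresholds at one value c.

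Mean = (17 × 22.6 + 13c)/30. SD = √{[16 × 2.9² + (17 × 13/30)(22.6 − c)²]/29}.

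- c = 18: mean = (384.2 + 234)/30 = 20.6, so 22.6 is 2.0°C too warm. SD = √[(134.6 + 155.9)/29] = 3.2.
- c = 12: mean = (384.2 + 156)/30 = 18.0, so 4.6°C too warm. SD = √[(134.6 + 827.7)/29] = 5.8.
- c = 20: mean 21.5, so 1.1°C too warm. SD 2.5.

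If non-achievers were cooled to 18°C and their thresholds lie between 12 and 18°C, the gap is 2.0 to 4.6°C. The last line shows that the SD is not certain to be understated if thresholds cluster at a warmer value.

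**4. Censored-normal fit.** With 17 exact values and 13 known only to be below c, the log-likelihood is

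−17 log σ − [16 × 2.9² + 17(22.6 − μ)²]/(2σ²) + 13 log Φ((c − μ)/σ).

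| Floor c (°C) | Mean | SD | 22.6 minus mean |
|---|---|---|---|
| 16 | 17.8 | 6.3 | 4.8 |
| 18 | 19.1 | 4.9 | 3.5 |
| 20 | 20.2 | 3.8 | 2.4 |
| 22 | 21.2 | 3.0 | 1.4 |

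**5. Cross-check by truncated-normal moments.** Match the proportion 17/30, the mean 22.6 and the SD 2.9, leaving the cut-off free. The standardised cut-off is −0.168, the mean shift is 0.694 SD, and the SD ratio is 0.634. Then σ = 2.9/0.634 = 4.6, μ = 22.6 − 0.694 × 4.58 = 19.4, and the cut-off is 19.4 − 0.168 × 4.58 = 18.7°C. The gap is 3.2°C, and the implied cut-off is close to the 18°C target.

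**6. Precision of an all-participant estimate.** Simulating 74 participants under these normal models and fitting the censored likelihood gives a 95% half-width of about 1.1 to 1.3°C, against 0.9°C for the conditional mean.

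**The case against.** The strongest reply is that the outcome is openly conditional. Section 5.i puts the proportion first and confines the temperature to those who reach ECI, so nothing is hidden or miscalculated. Non-achievers are not dropped from the study: they are in the proportion, and sections 5.ii and 8 compare them with achievers. One stated reason for the study (section 2.ii), avoiding hypothermia beyond the point of ECI, concerns achievers only. All of this stands. It is why the point is about what the mean can be used for, and not about an error in it.

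The size is also open to challenge:

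- The temperatures non-achievers reached are not given.
- Section 2.i requires 3 minutes below 2 µV. It also says that time to ECI and cortical temperature cannot be predicted precisely from the probes used, so some non-achievement may reflect cooling time or lag between probe and cortex.
- The normal model is rough. With an 18°C floor it puts about 11% of thresholds outside 12–28°C (7.5% below, 3.5% above), and with a 16°C floor about 23%.
- A censored analysis needs non-informative censoring, which the protocol does not allow us to check.

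These limits apply to the number of degrees. The mean still moves colder as long as non-achievers' thresholds are on average below 22.6°C, which a cooling target of 18°C makes likely.

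A reader might infer that the achievers' 95% interval fails outright, since in simulations it never covered the all-participant mean. That only tests an interval for one quantity against another in data built to separate them. It is not evidence that the interval is wrong for the conditional mean.

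**Conclusion.** The point holds as a limit on interpretation. The achievers' mean and SD are correct for achievers. They do not estimate the temperature needed for ECI, or its variation between neonates, which the aim, the introduction and the analysis section look to them for. Read that way, 22.6°C is too warm and the SD of 2.9 probably too small.

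The illustrative size is 2.0°C with every non-achiever's threshold at 18°C (SD 3.2), and about 3.5°C under a censored-normal model with an 18°C floor (mean 19.1, SD 4.9). Under that model it is 1.4 to 4.8°C for floors from 22 to 16°C. All of these exceed the 0.9°C half-width. They rest on the assumed floor and on non-achievement reflecting a colder threshold.

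A reader might go further and conclude that the true mean is established to be several degrees colder, or that section 7 is wrong. The documents support neither: the floor is not stated, and the section 7 arithmetic reproduces for the quantity it names.

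**What to change.** **Sections 5.i and 8.** Keep the proportion. Label the achievers' mean and SD as *conditional on reaching ECI before DHCA*. Add an analysis of all participants with a usable recording, with non-achievers censored at their own lowest recorded pre-DHCA temperature. Use Kaplan-Meier on the descending temperature scale to give the cumulative proportion in ECI by temperature and the median with a 95% CI. Use a censored-normal fit as sensitivity analysis. Each child's own lowest temperature then replaces the assumed floor used above.

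State two assumptions: that censoring is non-informative, and that some non-achievement may reflect cooling time or probe-to-cortex lag. With 41/74 = 55% reaching ECI the median should be estimable. Its colder confidence limit may not be, because the 95% CI for that proportion is about 0.55 ± 1.96 × √(0.55 × 0.45/74) = 0.44 to 0.67. The text should say how this will be reported.

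**Section 7.** State that ±0.9°C applies only to the conditional mean, and that the all-participant estimate would be less precise (about ±1.1 to 1.3°C under a normal model, marked as illustrative).

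**Cost.** Wording in three sections, a modest amount of extra analysis and a slightly wider stated interval. Section 4.i already provides for EEG in all participants and for recording of temperature, so no new data are needed. No change to cooling practice is implied.
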